### Recruitment

The catchment area of each Suraj SF centre covers a population of approximately 20,000–25,000 [31]. Each centre has an associated field health educator (FHE) who conducts door-to-door visits for family planning counseling [32]. These FHEs will recruit study participants through their routine door-to-door household visits. FHEs will liaise with lady health workers (LHWs), where possible, to help identify eligible participants. To ensure confidentiality and privacy, LHWs will take consent from potential 0participants before disclosing any information to the FHEs for screening and baseline interviews. FHEs will register all eligible women within their catchment areas on a standard data recording format. The final sample will be equally distributed across the study sites (*Suraj* SF centres). Based on vital statistics from Pakistan, it is estimated that recruitment take approximately three to four months.

FHEs will conduct initial eligibility screenings for potential participants during their door-to-door visits. This screening will include the following: age, pregnancy status, self-reported gestational age, and household literacy. If no one in the household, including the potential participant, is literate she will not be considered able to provide informed consent.

Following this screening, FHEs will obtain informed consent from women meeting the pre-consent eligibility criteria. Potential respondents will receive a detailed explanation of the study and their right to participate or refuse participation. FHEs will record all refusals and reasons for refusal. The FHE will give a verbal introduction to the potential participant and will talk them through the written consent form and obtain the participants agreement and signature. We will show a few text messages and play voice messages to the participants for understanding of the exposure to information. The study participant will be offered a copy of the signed consent form to keep for themselves if they wish. A thumb-print consent will be obtained in situations where the woman is not able to provide a signature. If a participant is under 18 years of age, the signed consent form will be taken from the guardian. More specifically, take consent from husband (if available and above 18 years) or mother-in-law or the head of household present at home at the time of interview. We will re-visit if parent or guardian is unavailable during FHE’s visit. We will ensure maintenance of confidentiality for each study participant in order to protect their rights and welfare. All the study participants will be informed about the purpose of study, follow-up mechanism, potential risks and benefits relating to their participation in the study. Study participants will also be given explanation about pregnancy test while taking consent. The result of pregnancy test will not be disclosed to any person other than the respective woman. Moreover, study participants will be reminded and reserve a right to decline answering any question(s) or quit during the interview at any point. All the study participants have the right to choose to partake in the study or refuse to participate and their refusal will not affect their right to MSS services. The study staff will be instructed to record all refusals and to attest to obtaining informed consent from the study participants. The signed consent form refers to all stages of the study (baseline, follow-up counselling, and post-delivery interview at Day-60); however, participants will have a right to withdraw or refuse to participate in the study at any point during the study period. Moreover, before each follow up interview the participants will be offered the opportunity to reread the consent form and the enumerator will check that the participant still agrees to take part in the study.

Women who provide informed consent will be asked to complete a post-consent eligibility assessment including a pregnancy test, access to a mobile phone, and willingness to receive health messages on their mobile phone. Women who meet this eligibility criteria will be enrolled in the study and administered the baseline interview.

### Assignment to intervention or control

Researchers will create a randomization sequence in permuted block sizes of three, six, and nine stratified by the Suraj SF using the *ralloc* command in Stata version 14.1. A specialized computer program (front-end interface) will be developed in Visual FoxPro version 7.0 that will be linked with the randomization database and stored in Stata. This database will be inaccessible to the research assistant who will control the allocation of participants to treatment groups.

After recruiting a participant for the study, FHEs will contact the research assistant by phone for the randomization process. The research assistant will collect preliminary information about the study participant, enter it into the pre-designed software mentioned above, and hit an icon to allocate the participant to a study group. Participants’ information will be sequentially stored in the randomization database. The research assistant will convey the assigned study group to the FHE. To prevent biases, only the principal investigator will have access to the randomization database and will not be involved in the allocation process.

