### Study design

PPFP is designed as a three-arm randomized controlled trial across 15 MSS’ social franchise health facilities.

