### Concomitant care

The government of Pakistan has a lady health worker (LHW) program operating across the country that also aims to increase contraceptive uptake. However, as participants in the study will be randomized at the individual level, the project team does not expect the LHW program to influence the results of this study. We will capture data on interactions that the participants may have with the LHWs, and subsequently, use it as a control variable in the analysis.

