### Sample size

An estimated sample size was extracted for each of the research questions. First, we estimated the sample size for the second hypothesis which was based on testing non-inferiority between text/voice messages and interactive phone calls. Non-inferiority tests require relatively higher sample sizes compared to superiority trials. We calculated a sample of 840 (420 in each group) using the following assumption: a non-inferiority margin of ten percentage points (from 25 to 15%) in the use of postpartum contraception within 42 days, 80% power, 0.025 level of significance (one-sided test), 2% missing data/non-response, 8% lost-to-follow-up^1^, and 20% aggregated chance of abortion/miscarriage/fetal loss. We found that an additional sample of 130 sample would be required in the control arm to detect an increase of 15%-points (from 18% [30] to 33%) in the use of PPFP between mobile supported interventions and standard care. This was estimated by using a pre-determined sample of intervention arms (i.e. 420), 0.05 level of significance, while holding other parameters constant. PASS version 11.0 was used for sample size calculation.

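### The sample size calls for arms of 420, 420 and 130, but blocks of three, six and nine over three arms allocate 1:1:1; the two sections must be reconciled.

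*Protocol article*

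**What the plan says.** The Study design section describes the trial as follows: "PPFP is designed as a three-arm randomized controlled trial across 15 MSS’ social franchise health facilities". Concomitant care confirms that the unit of allocation is the woman: "as participants in the study will be randomized at the individual level".

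The Sample size section first sizes the non-inferiority comparison of messages with calls: "We calculated a sample of 840 (420 in each group) using the following assumption". The assumptions include "a non-inferiority margin of ten percentage points (from 25 to 15"%), 80% power, a one-sided level of 0.025, and losses of 2%, 8% and 20%. It then turns to the comparison with standard care, 18% versus 33%, and finds that "an additional sample of 130 sample would be required in the control arm". On how that figure was obtained it says: "This was estimated by using a pre-determined sample of intervention arms (i.e. 420), 0.05 level of significance, while holding other parameters constant".

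The section Assignment to intervention or control fixes the allocation method: "Researchers will create a randomization sequence in permuted block sizes of three, six, and nine stratified by the Suraj SF".

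No section gives an allocation ratio in words, a total sample size, a weighted block composition, or a plan to close the control arm before the others. The Recruitment section spreads the sample equally over the sites; that sentence is about sites, not arms.

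**The concern.** The arm sizes are deliberately unequal, since the control arm is less than a third of either intervention arm. The block sizes are the multiples of three that one uses for equal allocation to three arms. A team that follows the allocation section cannot arrive at the arm sizes in the Sample size section without a departure that the article does not describe.

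The comparison most exposed is non-inferiority of messages to calls. It is one of the three primary objectives, and it sets the size of the intervention arms. If the total is held at 840 + 130 and split equally, women move out of the intervention arms, where that comparison needs them, and into a control arm that was planned to be small. If the control arm were instead closed once it reached 130, part of the intervention recruitment would have no concurrent controls, and the comparison with control could be confounded with calendar time.

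**Working it through.** **Inputs** (Sample size section unless stated): 25% use in both intervention arms; margin 10 points; one-sided 0.025; power 80%; losses 2%, 8% and 20%; 18% versus 33% for control against intervention at level 0.05; three arms (Study design); blocks of 3, 6 and 9 (Assignment to intervention or control). Two inputs are assumptions. The evaluable share is 0.70 if the losses are added, or 0.98 × 0.92 × 0.80 = 0.721 if they are multiplied. The 0.05 test is taken as two-sided because that reproduces 130.

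**1. Reproduce the 420.** n = (1.960 + 0.842)² × 2 × 0.25 × 0.75 / 0.10² = 294.3 evaluable per arm. Divided by 0.70 this is 420. Rounding up to 295 first gives 422 with added losses and 409 with multiplied losses. The stated figure reproduces.

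**2. Reproduce the 130.** With the intervention arm fixed at 294 evaluable (420 × 0.70), the smallest control arm giving 80% power for 18% versus 33% (two-sided 0.05, pooled-variance z test) is 89, and 89 / 0.70 = 128 after rounding up. With the intervention arm at 420 and a continuity correction it is 91, and 91 / 0.70 = 130. One-sided 0.05, with the intervention arm at 294 to 420, gives 67 to 108 and does not fit. So 130 is the whole control arm, not an addition to a control arm of 420.

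**3. The planned ratio.** 420:420:130 is 3.23:3.23:1, and 420 + 420 + 130 = 970.

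**4. The ratio that the blocks give.** A block of three holding three arms has one place per arm. A constant ratio across blocks of 3, 6 and 9 must be a multiple of that block: 1:1:1, 2:2:2, 3:3:3. A block of nine alone could hold 4:4:1, but a block of three could not. A 3:3:1 ratio needs blocks in multiples of 7.

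**5. Power under each reading.** Non-inferiority power = Φ(0.10 / √(2 × 0.25 × 0.75 / n) − 1.960), with n evaluable per arm. Power against control uses the pooled-variance z test, two-sided 0.05. Where a range is given, it runs from added to multiplied losses.

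| Allocation | Randomised (messages:calls:control) | Evaluable per intervention arm | Non-inferiority power | Power against control |
|---|---|---|---|---|
| As sized, 970 | 420:420:130 | 294–303 | 80–81% | 81–82% |
| 1:1:1, 970 | about 323 each | 226–233 | 69–70% | about 96% |
| 1:1:1, 1,260 | 420 each | 294–303 | 80–81% | about 99% |
| 3:3:1, 970 (added losses) | about 416:416:138 | 291 | 79.6% | about 83% |

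For the second row: 970 / 3 = 323.3; × 0.70 = 226.3; the standard error is √(0.375 / 226.3) = 0.0407; 0.10 / 0.0407 − 1.960 = 0.497; Φ(0.497) = 0.69.

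For the third row: 3 × 420 = 1,260, which is 290 more than 970.

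**The case against.** The strongest reply is that the arm sizes are the numbers required for each question, that is, minimums. Equal allocation continued until each arm has 420 meets all of them, with non-inferiority power of 80–81% and power against control of about 99%. A reader might therefore infer too much in saying that the randomisation cannot reach the stated power. That is right, and the stronger reading should not be made. What cannot coexist is equal blocks and arms of 420:420:130.

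Second, neither 970 nor 1:1:1 appears in the article. The ratio follows tightly from the block of three. The total is weaker: it is 840 + 130, and the figure of 69–70% depends on recruitment stopping there.

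Third, reporting only the loss would be one-sided. Two of the three primary objectives are comparisons with control, and under 1:1:1 at 970 they gain power. Power shifts from one question to the others.

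Fourth, a reader might infer that recruitment would stop in every arm once control reached 130. Nothing supports that, since the article asks for 420 in each intervention arm. Early closure of control is not proposed either. With recruitment of three months (Study setting) or three to four months (Recruitment), drift would be limited, and the comparison could be restricted to women randomised concurrently at some cost in power. One can say only that early closure could confound it.

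None of this reconciles the two sections. This is also not a detail left to a fuller document, because the article states both the arm sizes and the block sizes, and they conflict.

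**Conclusion.** The contradiction stands. The Sample size section and the section on assignment imply different allocation ratios, about 3.2:3.2:1 and 1:1:1, and no other section resolves them. Both 420 and 130 reproduce from the stated assumptions, so neither looks like a misprint.

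The size depends on what is done. With 970 women allocated equally, non-inferiority power is about 69–70%, roughly 10 to 11 points below the stated 80%, and power against control is about 96%. With 1,260 women allocated equally, the stated power is kept. These figures rest on the article's own rates and margin, 25% in both intervention arms, total losses of 28–30%, a two-sided 0.05 test against control, and an inferred total of 970. They do not show that the trial is underpowered; they show that a reader cannot tell which trial was planned, and that one natural reading falls short on the non-inferiority objective.

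**What to change.** State the allocation ratio and the total sample size, and make the two sections agree.

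- **If unequal allocation is intended**, use blocks that carry it. One example is 3:3:1 (messages:calls:control) within site in randomly ordered blocks of 7 and 14. At 970 women this gives about 416:416:138, slightly under 420 and 80% (79.6%), with about 83% power against control. To reach 420 in each intervention arm at this ratio takes 980 women (420:420:140), 10 more than 970.
- **If 1:1:1 is intended or was used**, say so and restate the arm sizes, the total and the non-inferiority power: about 69–70% at 970, or 80–81% at 1,260, which is 290 more women.

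Before recruitment, the first option costs a new allocation list and a corrected sentence. The article dates data collection, including recruitment, to March 2018 to March 2019, and it was published in August 2019, so allocation may already be complete. In that case the change is to reporting only: give the ratio actually used, the number randomised to each arm, and the resulting power or precision for the non-inferiority comparison. If the control arm closed before the others, say so and base the control comparison on women randomised concurrently.

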### Data collection

Data will be collected through face-to-face interviews using a structured questionnaire. FHEs will collect participants’ contact information (complete address and telephone number) during recruitment to reach them for the final interviews. This personal data will be stored separately from the interview data.

FHEs will complete data collection at baseline while external enumerators will conduct the final interviews to minimize interviewer biases. All data collectors will undergo comprehensive training on how to approach clients and build rapport; research ethics; data collection; interview techniques; the structured questionnaire; asking and eliciting responses on sensitive topics such as violence; administering and reading pregnancy tests; and the study protocol. Trainers will utilize class-room based training and role play to train data collectors and utilize quizzes affirm comprehension of study procedures.

### Data collection tools

PPFP uses structured questionnaires for data collection at baseline and endline. These questionnaires are expected to take 30–40 min to complete. All data collection tools will be developed in English and later translated to Urdu. The baseline questionnaire will be pre-tested with a cross-section of 20 women from areas comparable to the study sites while FHEs will identify women in their catchment areas who have given birth over the past 12 months to test the follow-up questionnaire. FHEs will obtain consent from women who participate in pre-testing the tools. The tools will be revised based on feedback from pre-testing.

#### Baseline questionnaire

The baseline survey questionnaire is comprised of six sections: a) socio-demographic factors, b) household decision making, c) social support to women, d) reproductive history, e) health seeking behaviors, f) domestic violence, g) knowledge about maternal and newborn health, and h) psychometric assessment regarding contraception. The psychometric tool (section H) will be developed based on finding from a previous qualitative study by MSS with postpartum women. Rest of the sections were previously developed under different studies. Questionnaires in English and Urdu can be found in Additional file 1 and Additional file 3, respectively. FHEs will conduct the baseline interview with participants during their door-to-door visit after completing the eligibility assessment and informed consent process.

Since it is difficult to implement five-point scales in low-literacy settings, we will be using the two-question method. For example, if the scale was “Strongly disagree 1 2 3 4 5 Strongly agree”, the data collector would ask two questions: “Do you agree or disagree?” then “Is your agreement/disagreement complete or partial?” Asking questions in this way will generate the necessary five-point scale in a more comprehensible manner for the population in concern.

#### Endline questionnaire

Endline data collection will take place two months (60 days) after delivery to allow women an additional 15 days after the postpartum period to adopt a contraceptive method as most women are confined to their homes during that time [33]. Prior to the follow-up, enumerators will contact participants to arrange a suitable time and place to conduct the interview. This interview will cover: a) clients’ experiences of childbirth, b) use of essential postpartum and postnatal care; c) contraceptive use and side effects; d) social support during the postpartum period; e) method continuation or reasons for discontinuation or method switching; f) reasons for not adopting contraception, g) pertinent future intentions, and (h) the psychometric assessment. Questionnaires in English and Urdu can be found in Additional file 2 and Additional file 4, respectively. Additionally, enumerators will gather feedback on both interventions from participants.

### Data management

The research team at MSS will be responsible for data management throughout the duration of this study. Researchers will develop the data entry software on Epidata version 3.1 with built-in validation checks to minimize errors in data. Two data operators will complete dual data entry at the MSS head office. Hardcopies of the questionnaires will be sorted according to a unique identifier and stored in assigned cabinets. Enumerators will retain a copy of participant contact sheets that will be used to conduct follow-up visits. Additionally, researchers will maintain a record of (home- or telephone-based) counselling sessions conducted by field health educators and will be monitored during visits by the research team.

### Analysis of psychometric data

Psychometric data will be first subjected to a Confirmatory Factor Analysis (CFA) to confirm the measurement validity of the constructs. Scales for the constructs will be refined if the model produces a low goodness of fit. Subsequently, reliability of the final scales will be tested through Ordinal Alpha, Coefficient H, and Composite Reliability, while CFA will establish the validity of the scales. Once the scales’ psychometric properties are confirmed to be reliable and valid, we will the validate the final behavioural model for post-partum uptake of modern contraception through Structural Equation Modelling (SEM).

### Data monitoring

The principal investigators and research team will closely supervise activities throughout the intervention and study period. Data collection tools will be translated under the close supervision of the principal investigator for accuracy. To ensure data quality, the principal investigator will conduct trainings for the enumerators. Additionally, the PI and study coordinator will regularly monitor adherence to study protocol and data collection processes.

During the study period, the research team will re-interview between two and 3 % of participants with shortened questionnaires at both time points. Intra-variability of interviewers will be tested by comparing data collected by the research team and the enumerators. If inconsistencies are noted, the research team will conduct a refresher training for enumerators. Finally, use of dual data entry will assure accurate entry and identify data entry operators who are routinely inconsistent.

### Harms (Adverse Events)

#### Risks to participants

As family planning is considered a taboo in Pakistan women often receive contraceptive services without informing other household members, making loss of confidentiality a potential risk for study participants. Conducting baseline and follow-up interviews at clients’ homes may, therefore, lead to a loss of confidentiality. To mitigate this risk, enumerators will take consent from participants to conduct household-based interviews at the time of enrolment. Further, participants will have the option to select another, more private location to complete the interviews. Participants will have time to discuss participation with the heads of the household (mother-in-law or husband) prior to enrolment.

The use of mHealth approaches further increases a possible breach of confidentiality as it is possible for a husband or other family member to answer a phone call, hear a voice message or see a text message and provoke negative reactions. To prevent this, enumerators will ask participants a series of questions including whether it is acceptable to contact them on their mobile phone (via message or call), who owns the mobile phone, if a certain time during the day is more suitable to receive messages or calls, and whether their husband is aware of their use of or interest in family planning methods. It is pertinent to note that voice messages and interactive phone calls will be completed solely by females. Additionally, the organization’s name will be reflected in the voice and text messages to avoid any ambiguities that may occur from anonymity. Lastly, in the case of the interactive phone calls, if the call is answered by someone other than the participant – the health worker will discuss issues related to general health.

The most recent DHS report (12, 13) revealed that the most common form of violence in this context is husbands’ desire to know the whereabouts of their wife and jealousy if they talk to other men. This study addresses these by completing interviews in the household setting and ensuring females complete all voice messages and phone calls. Though chances are minimal, in the case of intimate partner violence (IPV) participants will be connected to local organisations that provide IPV services such as PANAH Shelter and Madadgar. During recruitment, enumerators will ask participants to contact MSS (i.e. helpline, FHE, project team) in the case of IPV to seek help and/or to discontinue the study. A member of the MSS Health Services Department (HSD) will be nominated to document and track any reports of IPV amongst participants and report this to the project staff along with the appropriate actions to take.

Study participants may experience side effects from the contraceptive methods. This, however, is a risk due to contraceptive use and not due to their participation in the study. Study participants experiencing severe complications will be connected to a nearby MSS service provider for follow-up care.

Lastly, participants may choose to stop receiving messages or phone calls from the counsellor at any point during the intervention. They may contact the field health educator, the MSS helpline, respond to a text message to cancel subscription or contact the research coordinator to discontinue participation. Participants will receive monthly reminders on how to opt-out of the intervention.

